### Sample size {14}

The reviewed clinical trials and meta-analyses have consistently shown that 65% of patients receiving prophylactic the fluoroquinolones levofloxacin and ciprofloxacin will develop infectious fever (2,17,18) which is consistent with success rate of 35%. Considering that the actual rate of resistance to fluoroquinolones is established to be around 50%, we anticipate a success rate of 17% and 30% in the active control and active and experimental control arms, respectively.

If a non-inferiority margin of 5% is defined, one hundred and thirty-four patients (67 in each arm) will be needed to demonstrate non-inferiority of fosfomycin versus ciprofloxacin with 80% potency and an alpha level of 0.05.

Considering that 15% of the enrolled patients will be ineligible or unable to be evaluated, the maximum number of study participants will be 156: 78 patients in each arm.

### Recruitment {15}

There were strategies for achieving adequate participant enrolment to reach the target sample size.

Patients who are undergoing HSCT will be previously evaluated in the pre-transplant consultation while patients diagnosed with acute leukemia will be evaluated during the first days of hospitalization. Based on whether they meet the selection criteria of the FOVOCIP study protocol, they will be asked to participate in the study by signing the informed consent form.

## Assignment of interventions: allocation

### Sequence generation {16a}

The randomization will be carried out by the electronic clinical registry (eCRF) called MACRO. The management of the electronic tool is carried out by the SCReN clinical research platform work-package.

After inclusion, the randomization list included in the eCRF will automatically assign the case to the control or experimental group in 1:1 ratio. Candidates are stratified according to their baseline disease: acute leukemia or HSCT.

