### Trial design {8}

The FOVOCIP study is a randomized, open-label, phase III clinical trial with a non-inferiority design, in which patients are randomized in a 1:1 ratio into two parallel, controlled prophylaxis groups: fosfomycin or ciprofloxacin. The groups are stratified by site and by underlying disease (acute leukemia or stem cell transplantation).

FOVOCIP is a pragmatic study and very well adapted to the usual clinical practice of the sites of the public health system in Spain.

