#### Outcomes {12}

The primary endpoint is febrile neutropenia requiring antibacterial treatment.Fever is defined as a single oral temperature of 38.3 °C or a temperature of 38 °C sustained over a 1-h period.

If the patient is receiving any medication highly likely to induce fever or has previously received a transfusion, at least one positive culture or infectious focus will be required for fever to be attributed to infection.

When febrile neutropenia occurs and infection is suspected, prophylactic antibiotics will be discontinued and evaluation and therapy will be administered according to standard and local guidelines.

Secondary endpoints are as follows:Documented infections. They will be classified according to Han’s criteria in one of these categories: microbiologically documented infection (bacterial viral or fungal), mixed infection, clinically documented infection, and possible infection (fever of unknown origin).The amount of concomitant antibiotics prescribed in addition to prophylactic drugs will be measured as a ratio of antibiotic days per days of hospitalization. Antibiotics will be classified according to the watch/reserve classification (21).Overall survival will be defined as the time from the day of randomization to the date of death (whatever the cause of death) or to the completion of the study. Fever-free survival will also be determined.

Safety will be assessed by the incidence, severity and type of adverse events (AEs), and by the microbiological assessments:

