## Statistical methods

### Statistical methods for primary and secondary outcomes {20a}

This phase 3 trial will compare the efficacy of fosfomycin with that of ciprofloxacin in preventing the occurrence of at least one episode of neutropenic fever of infectious origin in a randomized non-inferiority design.

The primary endpoint is febrile neutropenia of infectious origin. This analysis will be performed in the intention-to-treat (ITT) and in the per-protocol population (PP). The ITT population is defined as all patients who are eligible and randomized. The PP population consists of all patients who do not have major protocol deviations, as determined by the study PI, and have received prophylactic drugs for at least of 24 h.

The rate of febrile neutropenia will be compared between the 2 arms with a chi-square test with 2-sided alpha of 0.05. The difference in the proportion and the associated 95% CIs will be provided. If, within either patient arm, the data suggest a possible difference in baseline incidence between the randomization strata, we will consider Cochran-Mantel–Haenszel test to examine the association between the incidence of febrile neutropenia and the study treatment with adjustment for the randomization strata. Logistic regression models will be performed to evaluate the treatment effect on the incidence of febrile neutropenia adjusting for stratification and other baseline patient characteristics.

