The analysis of the secondary endpoints will be performed as follows:Rate and type of documented infections with 2-sided alpha of 0.05. Again, logistic regression models will be performed to evaluate the treatment effect on the incidence of each event adjusting for stratification and other baseline patient’s characteristics.Amount of concomitant antibiotic utilization. The analysis will be performed with a 2-sample *t*-test or the Mann–Whitney *U* test if the distribution is non-normal.Survival will be analyzed using the Kaplan–Meier estimate. The K-M survival curves and medians (if estimable) along with their 2-sided 95% CIs will be provided for each treatment arm. The log-rank test will be used to compare treatment arms. Differences in survival without fever will also be assessed with a log-rank test at the 5% significance level.Adverse events. This end point is included in the safety analysis and will be performed in the SP. AE will be categorized as severe and non-severe, as this classification determines the notification procedure. Intensity of AE will be evaluated according to the National Common Terminology Criteria for Adverse Events (NCI CTCAE), version 5.034.

The microbiological safety assessments will be analyzed as specified in item 33.

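### Randomisation is stratified by disease group, but the named tests for survival, survival without fever and antibiotic use carry no stratum; if disease group is prognostic, these secondary comparisons are conservative and lose some power

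*Protocol article*

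**What the plan says.** All references are to the protocol article.

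- **Randomisation.** Sequence generation {16a}: "Candidates are stratified according to their baseline disease: acute leukemia or HSCT". Trial design {8} adds a second factor: "The groups are stratified by site and by underlying disease (acute leukemia or stem cell transplantation". Both sections include disease group; only Trial design includes site.
- **Survival.** Statistical methods {20a}, on overall survival: "The log-rank test will be used to compare treatment arms". Outcomes {12} adds a further time-to-event endpoint: "Fever-free survival will also be determined". Its test is given in {20a}: "Differences in survival without fever will also be assessed with a log-rank test at the 5% significance level".
- **Antibiotic use.** "The analysis will be performed with a 2-sample" t-test, or a Mann-Whitney test if the distribution is not normal.
- **Where stratification is used.** For documented infections, "logistic regression models will be performed to evaluate the treatment effect on the incidence of each event adjusting for stratification and other baseline patient’s characteristics". The primary endpoint has a similar adjusted logistic model and a conditional option: "we will consider Cochran-Mantel–Haenszel test to examine the association".

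No stratum is named for the three comparisons at issue.

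**The concern.** Stratified randomisation removes chance imbalance in disease group between the arms. If disease group affects the outcome, a test that leaves it out still counts the between-group spread as random error. The standard error is then too large, the true type I error falls below the stated 5%, and real differences are missed more often.

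A difference between the groups is plausible. Leukemia patients receive a first intensive chemotherapy course, and the others an allogeneic or autologous transplant. The plan itself allows for different febrile neutropenia incidence between strata when it keeps the Cochran-Mantel-Haenszel test in reserve.

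Conservatism is not wholly harmless in a non-inferiority trial. A secondary test that misses a real difference in time to fever makes the arms look alike, which favours the conclusion the trial hopes to reach.

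**Working it through.** **1. The plan's own figure.** Sample size {14} takes success rates of 17% and 30%, a margin of 5 points, 80% power and alpha 0.05. With one-sided 0.05:

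n per arm = (1.645 + 0.842)² × (0.17×0.83 + 0.30×0.70) / (0.13 + 0.05)² = 6.18 × 0.3511 / 0.0324 ≈ 67.

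This reproduces 67 per arm. Then 67 × 1.15 = 77.05, rounded up to 78 per arm, gives 156. The article states no power, event count or hazards for the three secondary endpoints, so what follows rests on assumptions.

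**2. Antibiotic use, by formula.** Assume two equal disease groups, arms balanced within each, within-group SD 1 and a shift of d SD between groups. The true standard error of the arm difference is 2/√156 = 0.160. The t-test uses a variance of 1 + d²/4, so its critical value is in effect 1.96 × √(1 + d²/4). For an assumed treatment effect of 0.45 SD, 0.45/0.160 = 2.81. Type I error is 2 × [1 − Φ(critical value)]; power is Φ(2.81 − critical value).

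| d | Critical value | Type I error (formula / simulated) | Power, t-test (formula / simulated) | Power, with group term (simulated) |
|---|---|---|---|---|
| 0 | 1.96 | 5.0% / 5.1% | 80% / 80% | 80% |
| 0.5 | 2.02 | 4.3% / 4.2% | 79% / 78% | 80% |
| 1 | 2.19 | 2.8% / 3.0% | 73% / 72% | 80% |
| 1.5 | 2.45 | 1.4% / 1.4% | 64% / 63% | 80% |

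Formula and simulation (8000 runs) agree. The Mann-Whitney test behaves like the t-test: simulated type I error 5.0%, 4.4%, 3.1% and 1.2%.

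**3. Survival without fever, by simulation.** Assumptions: 156 patients, 1:1, two equal groups, permuted blocks of 4 within group, exponential times, about 76.5% events, treatment hazard ratio 0.60, two-sided 5%, 6000 runs.

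| Hazard ratio between groups | Type I error, unstratified / stratified | Power, unstratified / stratified |
|---|---|---|
| 1 | 5.4% / 5.5% | 74.0% / 73.7% |
| 1.5 | 4.8% / 5.5% | 73.5% / 74.9% |
| 2 | 4.0% / 4.9% | 70.2% / 74.6% |
| 3 | 3.2% / 5.1% | 63.6% / 75.4% |
| 4 | 2.2% / 5.4% | 56.4% / 75.6% |

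A second simulation used a treatment hazard ratio of 0.65 and hazards set to about 82% fever in the control arm, close to the planned 83% (100% − 17%). It gave losses of 1 to 2 points at 1.5, 5 to 6 at 2 (type I error 4.1% against 5.0%) and about 13 at 3 (3.3% against 5.9%). In that last case the stratified test itself ran above 5%, so 13 is at the generous end.

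**4. Dependence on balance within strata.** With simple randomisation in place of blocks, the unstratified log-rank test stayed at 4.7% to 5.1% under the null for every ratio in the table. The conservatism therefore needs balance within strata as well as a prognostic factor.

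**5. Overall survival, same set-up.**

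| Events | Treatment hazard ratio | Ratio between groups | Type I error, unstratified | Power, unstratified / stratified |
|---|---|---|---|---|
| 10% | 0.30 | 2 | 5.0% | 40.4% / 40.8% |
| 10% | 0.30 | 4 | 4.6% | 40.7% / 41.9% |
| 30% | 0.50 | 1.5 | 4.7% | 51.8% / 52.0% |
| 30% | 0.50 | 3 | 3.9% | 51.6% / 54.0% |
| 45% | 0.55 | 1.5 | 5.2% | 60.3% / 60.8% |
| 45% | 0.55 | 3 | 3.8% | 57.8% / 62.5% |

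The loss runs from near nil to about 5 points.

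**The case against.** **The text is silent rather than wrong.** The article does not call the log-rank tests unstratified, and a full analysis plan, not shown, may add the stratum. A reader might infer that no stratified analysis will be done under any condition; the article does not say that. What remains is that specific tests are named, and that the same section states the stratification adjustment for other endpoints. The case is firmest for antibiotic use, where an ordinary t-test or Mann-Whitney test has no place for a stratum.

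**The loss is conditional.** A reader might infer that these tests simply run below 5% and lose power. That is unsupported: no outcome figures are given by disease group, no blocking scheme is stated, one success rate per arm covers both groups, and the Discussion describes the population as homogeneous. Autologous and reduced-intensity transplants also need an added infection risk factor to qualify, which may narrow the difference between groups. This objection stands and limits the point.

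**The larger losses might come from fever rates below the planned 83%.** This does not hold: with hazards set to about 82% control fever, the losses at each ratio are similar.

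**Impact is low.** The tests remain valid and err on the cautious side, all three endpoints are secondary, and febrile neutropenia already has an adjusted model. This stands and sets the priority.

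**Conclusion.** The mismatch between stratified randomisation and the three named tests is real, and any effect is in the conservative direction. Its size depends on two things the article does not give: how prognostic disease group is, and how well the arms are balanced within it.

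- **Survival without fever:** about 1 to 2 points of power at a between-group hazard ratio of 1.5, about 5 (4 to 6 across simulations) at 2, and 10 to 13 at 3; type I error about 4.8%, 4.0% and 3.2%.
- **Antibiotic use:** about 2 points at a 0.5 SD shift and 8 at 1 SD.
- **Overall survival:** 0 to 5 points, near nil with few events.
- **If the groups do not differ:** no loss.

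The error rate is not inflated, and neither the primary non-inferiority conclusion nor the 156 patients is touched. This is an optional efficiency gain for secondary endpoints, not a flaw that threatens the trial.

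**What to change.** In the secondary-endpoint part of Statistical methods {20a}:

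1. For survival without fever and, for consistency, overall survival, name a log-rank test stratified by randomised disease group (acute leukemia / HSCT), with the hazard ratio from a Cox model stratified the same way. Keep the Kaplan-Meier curves as planned.
2. For antibiotic use, replace the t-test with a linear model containing disease group, or use the van Elteren test where a rank test is preferred.
3. Reconcile Trial design {8} and Sequence generation {16a} on whether site is also a stratification factor. If it is, 11 sites by 2 groups makes 22 cells, about 156/22 = 7 patients each. That is too sparse to stratify the log-rank test by every cell, so disease group alone remains the practical stratum.

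The cost is one or two sentences before the data are analysed. Disease group is already used for randomisation in the eCRF, so no new data or patients are needed. If the full analysis plan already stratifies these tests, only the article's wording needs to match it.

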### Concealment mechanism {16b}

Allocation concealment will be ensured as MACRO will not release the randomization code until the patient has been recruited into the trial.

### Implementation {16c}

The patient assignment codes are made up of 4 digits. On the one hand is the hospital number, University Hospital Central of Asturias (number 01), Hospital San Pedro Alcantara (number 2), University Hospital Morales Messeguer (number 03), University Hospital La Paz (number 04), University Hospital Fundación Jimenez Diaz (number 05), University Hospital Clínico San Carlos (number 06), University Clinic Hospital of Valencia (number 07), University Hospital La Fe (number 08), University Hospital of Málaga (number 09), University Hospital Lozano Blesa of Zaragoza (number 10), and University Hospital of Burgos (number 11), and on the other hand is the consecutive number of the new patient included.

These codes are assigned by the CRF of the study.

## Assignment of interventions: blinding

### Who will be blinded {17a}

The study is open-label. The investigators and the patient are aware of the treatment administered. The project manager only knows the randomization list, so the investigator does not know the treatment that will be assigned to the patient until the candidate is randomized. The assessors and data analysts will be blinded.

### Procedure for unblinding if needed {17b}

The design is open label with only outcome assessors being blinded, so unblinding will not occur.

## Data collection and management

### Plans for assessment and collection of outcomes {18a}

To evaluate the primary and secondary variables of the study, vital signs (blood pressure, heart rate, temperature) will be checked during the physical examination at successive visits. Laboratory tests including blood count, biochemistry and coagulation, electrocardiogram (ECG), microbiological studies, and review of treatment will be performed.

### Plans to promote participant retention and complete follow-up {18b}

An end-of-treatment visit is made to coincide with the last dose of study medication (fosfomycin or ciprofloxacin). And a follow-up visit is scheduled 15 days after the last dose of treatment to perform physical examinations and record adverse effects, ECOG, concomitant treatment, electrocardiogram (ECG), laboratory investigations, and microbiological studies.

If the patient is unable to attend the follow-up visit, this can be done by telephone.

### Data management {19}

The MACRO® software is a data collection and study management application that uses a secure web browser. It provides access to clinical study data and management of the clinical study process.

The objective is that, at the end of the study, all the available forms are as follows:✓ Completed by the investigator✓ With no queries pending to be solved by the Investigators✓ With no queries pending to be closed by the CRAs/PMs✓ Verified by the CRAs✓ Locked by the PMs

### Confidentiality {27}

Personal data will be processed in accordance with Regulation (EU) 2016/679 of the European Parliament and of the Council of 27 April 2016 on the protection of individuals regarding the processing of personal data and on the free movement of such data and the relevant local laws.

The data collected for the study will be identified by an alphanumeric code in such a way that it will not be possible to identify the patient. Only the investigator and authorized persons involved in the study will have access to this code and use this information exclusively for the purposes of the study. All the generated data will be recorded in the eCRF in an anonymized form.

Members of the Clinical Research Ethics Committee or Health Authorities may have access to this information in compliance with legal requirements. The confidentiality of this data will be preserved, and it will not be linked to personal data, even if the results of the study are published.

### Plans for collection, laboratory evaluation, and storage of biological specimens for genetic or molecular analysis in this trial/future use {33}

All study subjects will be screened for MDRGN gut colonization by microbiological culture at the first visit and weekly thereafter during the neutropenic period, until study completion. In each participating center, rectal exudates will be collected in ESwab™ (Copan Diagnostics Inc., Murrieta, CA) that will be sent to the microbiology laboratories for culture in selective media for MDRGN, according to the recommendations of the Spanish Society for Infectious Diseases and Clinical Microbiology (SEIMC) (22,23), specifically in CHROMagar™ *Acinetobacter* (Biomerieux, Marcy l’Etoile, France), CHROMagar™ *P. aeruginosa* (Biomerieux), CHROMagar ™ ESBL (Biomerieux), and CHROMagar™ CARBA SMART (Biomerieux) and in Columbia Agar plate (Biomerieux) as a growth and sample quality control. The isolates recovered in the selective media will be identified by MALDI-TOF/MS (Bruker Daltonics, Bremen, Germany), and the antimicrobial susceptibility testing will be performed using the Microscan system (Beckman Coulter, Brea, CA) and interpreted according to the European Committee on Antimicrobial Susceptibility Testing (EUCAST) guidelines. Bacterial samples and isolates will be stored at – 80 °C.

The clinical trial includes a substudy in a population of 30 subjects, representative of the two treatment arms, both colonized and non-colonized according to the conventional microbiological techniques results. Two samples from each of these subjects will be recovered between those processed for culture (stored at – 80 °C) at the baseline visit and at the end of the study. In these samples, the evolution of the resistome will be investigated using “shotgun” metagenomic sequencing techniques. These results will be compared with those obtained by culture.

The patient’s microbiome evolution will be studied by metataxonomic sequencing. For this purpose, a fecal sample will be collected from each study subject at the baseline visit and at the end of the study.

Figure 1 shows schematically the clinical and microbiological study planning.

**Fig. 1 Fig1:**
[figure not shown]
Clinical and microbiological study planning

## Statistical methods

### Statistical methods for primary and secondary outcomes {20a}

This phase 3 trial will compare the efficacy of fosfomycin with that of ciprofloxacin in preventing the occurrence of at least one episode of neutropenic fever of infectious origin in a randomized non-inferiority design.

The primary endpoint is febrile neutropenia of infectious origin. This analysis will be performed in the intention-to-treat (ITT) and in the per-protocol population (PP). The ITT population is defined as all patients who are eligible and randomized. The PP population consists of all patients who do not have major protocol deviations, as determined by the study PI, and have received prophylactic drugs for at least of 24 h.

The rate of febrile neutropenia will be compared between the 2 arms with a chi-square test with 2-sided alpha of 0.05. The difference in the proportion and the associated 95% CIs will be provided. If, within either patient arm, the data suggest a possible difference in baseline incidence between the randomization strata, we will consider Cochran-Mantel–Haenszel test to examine the association between the incidence of febrile neutropenia and the study treatment with adjustment for the randomization strata. Logistic regression models will be performed to evaluate the treatment effect on the incidence of febrile neutropenia adjusting for stratification and other baseline patient characteristics.

The analysis of the secondary endpoints will be performed as follows:Rate and type of documented infections with 2-sided alpha of 0.05. Again, logistic regression models will be performed to evaluate the treatment effect on the incidence of each event adjusting for stratification and other baseline patient’s characteristics.Amount of concomitant antibiotic utilization. The analysis will be performed with a 2-sample *t*-test or the Mann–Whitney *U* test if the distribution is non-normal.Survival will be analyzed using the Kaplan–Meier estimate. The K-M survival curves and medians (if estimable) along with their 2-sided 95% CIs will be provided for each treatment arm. The log-rank test will be used to compare treatment arms. Differences in survival without fever will also be assessed with a log-rank test at the 5% significance level.Adverse events. This end point is included in the safety analysis and will be performed in the SP. AE will be categorized as severe and non-severe, as this classification determines the notification procedure. Intensity of AE will be evaluated according to the National Common Terminology Criteria for Adverse Events (NCI CTCAE), version 5.034.

The microbiological safety assessments will be analyzed as specified in item 33.

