#### Objective

The main objective of this clinical trial is to demonstrate non-inferiority in efficacy of oral fosfomycin versus oral ciprofloxacin in preventing febrile neutropenia in patients with acute leukemia treated with intensive chemotherapy and/or recipients of hematopoietic stem cell transplantation.

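### The primary comparison in section {20a} is a chi-square test of equality, and no rule ties the confidence interval to the 5% non-inferiority margin

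*Protocol article*

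**What the plan says.** - **Aim.** The Objective section states: "The main objective of this clinical trial is to demonstrate non-inferiority in efficacy of oral fosfomycin versus oral ciprofloxacin in preventing febrile neutropenia". Trial design {8} and the opening of section {20a} also call it a non-inferiority trial.
- **Margin and size.** Sample size {14}: "If a non-inferiority margin of 5% is defined, one hundred and thirty-four patients (67 in each arm) will be needed". The planning success rates are 17% on ciprofloxacin and 30% on fosfomycin, with 80% power and alpha 0.05 of unstated sidedness. Allowing for 15% loss gives 156 patients, 78 per arm.
- **Primary comparison.** Section {20a}: "The rate of febrile neutropenia will be compared between the 2 arms with a chi-square test with 2-sided alpha of 0.05".
- **Interval.** The next sentence reads: "The difference in the proportion and the associated 95% CIs will be provided". It mentions no margin.
- **Other analyses in the same section.** If baseline incidence appears to differ between strata, "we will consider Cochran-Mantel–Haenszel test to examine the association between the incidence of febrile neutropenia and the study treatment". In addition, "Logistic regression models will be performed to evaluate the treatment effect on the incidence of febrile neutropenia adjusting for stratification".
- **The margin elsewhere.** After the sample-size section, the 5% margin appears only in Interim analyses {21b}, in a rule for possible early termination if fosfomycin looks inferior.

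**The concern.** A non-inferiority claim requires rejecting the hypothesis that fosfomycin is worse by the margin or more. The chi-square in {20a} tests a different hypothesis, that the two rates are equal. A non-significant result is compatible with a loss well beyond 5 points, and a significant result shows only that the rates differ. The Cochran-Mantel-Haenszel test and the logistic models do not fill the gap: both assess association, and neither carries a margin on its scale. The 95% CI could answer the question, but it is only to be reported.

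At stake is the trial's main conclusion. The trial is open-label, so the rule that turns data into a conclusion should be explicit before readout. As the text stands, the one comparison given an alpha for the primary endpoint is the wrong one for the hypothesis.

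**Working it through.** **Inputs.** Success 17% (ciprofloxacin) and 30% (fosfomycin), which is fever in 83% and 70%; margin 5%; 67 per arm; power 80%; alpha 0.05 (all from Sample size {14}); two-sided alpha 0.05 and 95% CI (section {20a}). Two assumptions: the margin is absolute, in percentage points, and success is the complement of febrile neutropenia.

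**1. Reproduce the planned size.** For a margin-based test, n per arm = (z_alpha + z_power)² × [p1(1−p1) + p2(1−p2)] / (p2 − p1 + margin)².

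- Variance term: 0.17 × 0.83 + 0.30 × 0.70 = 0.3511. Distance from the margin: 0.13 + 0.05 = 0.18.
- One-sided 0.05: (1.645 + 0.842)² × 0.3511 / 0.18² = 67.0, so 67 per arm and 134 in total. This is the protocol's figure.
- One-sided 0.025: (1.960 + 0.842)² × 0.3511 / 0.18² = 85.1, so 86 per arm. No match.
- Test of equality at 17% vs 30%: 166 per arm two-sided, 181 with continuity correction, 131 one-sided. No match.

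Of these formulas, only the margin-based test at one-sided 0.05 gives 67.

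**2. Power of the named test.** With 67 per arm the standard error is √(0.3511/67) = 0.0724. For the two-sided chi-square, Φ(0.13/0.0724 − 1.96) = Φ(−0.16) = 0.43; exact binomial enumeration gives 0.429. The stated power is 80%.

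**3. Power of a margin-based rule at the same size.**

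| Rule | 67 per arm | 78 per arm |
|---|---|---|
| 90% CI (one-sided 0.05): Φ(0.18/SE − 1.645) | 80.0% | 85.0% |
| 95% CI (one-sided 0.025): Φ(0.18/SE − 1.960) | 70.1% | 76.5% |

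The SE for 78 per arm is √(0.3511/78) = 0.0671.

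**4. What non-significance would mean.** Exact binomial enumeration, 67 per arm, fever 83% on ciprofloxacin, pooled z test, Wald interval:

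| True fever rate on fosfomycin | Chi-square p > 0.05 | Upper 95% limit below +5 points |
|---|---|---|
| 88% (5 points worse, at the margin) | 87.4% | 3.0% |
| 93% (10 points worse) | 56.7% | 0.3% |

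The middle column is an error rate only if p > 0.05 is taken as non-inferiority. At the planning rates, 27% of trials would meet the 95% CI rule and still have a non-significant chi-square.

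**5. Two data sets (fevers out of 67, fosfomycin vs ciprofloxacin).**

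- 61 vs 56: p = 0.19; difference +7.5 points, 95% CI −3.7 to +18.7. Not significant, and non-inferiority not shown.
- 47 vs 56: p = 0.065; difference −13.4 points, 95% CI −27.5 to +0.7. Not significant, yet non-inferiority shown.

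The chi-square gives the same answer, not significant, to two data sets with opposite conclusions on non-inferiority.

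**The case against.** The parts of a non-inferiority decision are all in the article. Section {20a} calls the design non-inferiority and promises the difference in proportions with a 95% CI, with the primary analysis in both the intention-to-treat and per-protocol populations. The margin is prespecified in {14}, and {21b} uses it. A reader could place the interval against 5% unaided, and because the article condenses a fuller protocol, the linking sentence may exist elsewhere.

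Much of this stands. It means that the repair is short, and it rules out two stronger readings. A reader might infer that the trial as planned has no means of assessing non-inferiority; the promised interval shows otherwise. A reader might also infer that the sponsor intends to treat p > 0.05 as non-inferiority, so that 87% and 57% are the plan's actual error rates. No sentence says so; those figures describe a possible misreading. Nor is the chi-square the only analysis named, or the margin absent from everything after the sample size.

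What does not stand is the appeal to omitted detail. The article is not silent on the primary test: it names one, with its alpha and sidedness, and that test does not fit the stated hypothesis. The interim use of the margin concerns stopping for inferiority and gives no rule for concluding non-inferiority at the end.

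**Conclusion.** The point holds for section {20a}. The named primary comparison cannot establish non-inferiority, the accompanying interval is not tied to the margin, and the test does not match the calculation behind 67 per arm. At the planning rates its power is about 43% against the stated 80%. There is a second mismatch within the same text: the planned size corresponds to one-sided 0.05, whereas the 95% CI in {20a}, if used for the decision, corresponds to one-sided 0.025 and about 70% power with 67 per arm.

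These figures rest on an absolute 5-point margin, success as the complement of febrile neutropenia, normal-approximation sample-size formulas and Wald intervals. Because the issue governs the main conclusion, it should be corrected before the final analysis.

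**What to change.** In section {20a}, replace the chi-square as the primary test with a decision rule: non-inferiority is concluded if the upper limit of the CI for fosfomycin minus ciprofloxacin, in the proportion with febrile neutropenia, is below +5 percentage points. Keep a test against zero only as a subsequent superiority step, taken once non-inferiority is shown. This fixed order costs no alpha.

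State alpha in the same edit, by one of two routes:

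- **Keep the two-sided 95% CI (one-sided 0.025).** Restate the power as about 70% with 67 per arm, or about 77% with 78, in place of 80%. Restoring 80% would need 86 evaluable per arm (172); 86/0.85 rounds up to 102 per arm (204) after 15% loss.
- **Use a 90% CI (one-sided 0.05).** This matches the 80% power and 67 per arm in {14}, and should be stated and justified.

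The wording costs a few sentences and no new data. The substantive cost is either a less favourable stated power (or a larger trial) under the 95% CI, or a more lenient type I error under the 90% CI.
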